### Stage 2: RCT

After the completion of stage 1, the research team will contact each participant at intermediate cardiovascular risk to include those participants in the intervention stage. Participants will be randomised in the intervention group, e.g. behavioural change conducted by community champions or in the control group e.g. brief advice only.

First, the community champions will be trained in communication skills improvement based on motivational interviewing coaching. The first version of the training will be appraised by national experts in behavioural change and motivational interviewing and by members of the research team. Champions and members of the research team will try this version, comment on it and propose areas of improvement. The modified version of the training will be used for all the champions. The champions will be followed up individually and in groups from the beginning to the end of the study. Individual training for new champions is planned in the event of withdrawal. Champions will be assigned to geographical areas close to the residential areas of the participants.

Second, RCT intervention group participants will benefit from repeated brief advice every 6 months and motivational group sessions conducted by community champions. Each group session will last one and a half hours. Groups are expected to consist of 10 to 15 participants. The groups will meet 13 times during the 2 years of the study. During a first intensive phase, the groups will meet every 15 days (Day 0, D15, D30, D45, D60). Then, 2 meetings will be scheduled during the 2-month short maintenance phase (M3, M4); finally, a long maintenance phase with meetings every 3 months will last until the end of the study (M7, M10, M13, M16, M19, M21). Champions will use Motivational Interviewing techniques and adopt a support role in the group. Individuals in the group will work on behavioural micro-objectives and micro-changes. The study setting will be community halls loaned by local stakeholders. The research team will set up health conferences at least once, and up to four times, during the study for the participants, depending of the needs expressed by the community champions.

RCT control group participants will benefit from repeated brief advice every 6 months. Brief advice will be delivered as in the intervention group.

Implementation at this phase comprises quantitative and qualitative evaluation. Qualitative evaluation will comprise a profiling of the community champions, focusing on barriers and facilitators relating to follow-up, as perceived by the champions and the research team, by either focus-groups or individual interviews. A purposive sample of screeners will be created. Sampling criteria will include age, number of participants in group, location of follow-up. Data collection will continue until theoretical saturation of the data is reached. A thematic analysis will be performed. Two researchers, working blind, will code the data then merge their analyses.

#### Outcomes

The primary outcome will be the comparison of the NL-IHRS between the two branches of the study after 24 months.

The secondary outcomes after 24 months will be quality of life, as assessed by the WHOQOL-BREF [17], modification of diet, according to the DASH questionnaire [18], modification of physical activity, following the IPAQ-short [19], BMI reduction, smoking level, modification of self-declared alcohol consumption.
The WHOQOL-BREF questionnaire was derived from the WHOQOL-100 in 1996 to assess quality of life by using thirty-three questions within the four following domains: physical health, psychological domain, social relationships and environment.The DASH questionnaire was created in 2016 to assess, by means of eleven questions, the quality of an individual’s diet, according to the Dietary Approach to Stop Hypertension. This diet was designed along the lines of the Mediterranean diet to improve the cardiovascular risk profile of the consumers [20].The IPAQ was created in 2003 to assess physical activity. The short version comprises seven questions in four blocks which describe intense activity, moderate activity, walking in the last 7 days and time spent seated. The score of the IPAQ-short can be converted in Metabolic Equivalents of Task, a standardised measurement of physical activity level.

The tertiary outcomes will be the same as previously stated, assessed at 6 and 12 months. The implementation strategy will be assessed by mixed methods comprising qualitative research methods and quantitative descriptive epidemiological studies [21]. Quantitative implementation data collected at 12 and 24 months will consist of the number of people screened with the NL-IHRS, the number of people entering the behavioural change intervention, the number of people completing the entire intervention, the cost of the intervention. Qualitative studies will be constructed using the Re-Aim model [22], exploring invention barriers and facilitators and perspectives from screeners, community champions, stakeholders and members of the research team.

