**Methods:**

A two-step RCT hybrid type 1 implementation study will first of all screen a population using the Non-Laboratory INTERHEART Score (NL-IHRS) and will involve health-care students at public events in the COB area until 1000 participants have been recruited. Second, a RCT will be carried out. The research team will contact each participant with an intermediate NL-IHRS in order to include them. Participants will be over 18 years of age and work or live in the COB area. Participants will be equally randomised in two groups. The intervention group will receive brief advice plus behavioural change guidance carried out by community champions. The control group will receive brief advice only. The main objective for the RCT is to assess a difference of at least 15% in the NL-IHRS between the two groups after 24 months. The primary outcome will be analysed with intention to treat. Secondary outcomes for the RCT will be assessed using validated questionnaires: the WHOQOL-BREF, the DASH Q questionnaire, the IPAQ-short; smoking level will be assessed according to the NL-IHRS scoring system; a modified self-declared alcohol consumption questionnaire has been developed and gauges will be used to assess BMI. The implementation strategy will use mixed methods: qualitative research methods and quantitative epidemiological studies.

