### STAGE 1: general population screening and brief advice

Extensive screening of the population will be conducted, involving students undertaking national health service. They will use the NL-IHRS developed for use on a tablet, using the REDcap© software. REDCap© allows data collection in the field followed by secured internet transfer of the data. Standardised, appropriate, brief advice will be constructed following the items of the NL-IHRS score, based on the French healthy lifestyle recommendations edited by the Haute Autorité de Santé and Santé Publique France. The brief advice regarding smoking habits and stress and depression will be constructed following the expertise of the team’s addiction expert (MG). Each piece of advice generated will be standard but will only appear on the tablet when it fits the participant’s answer to the particular item in the score.

The screening study setting will be local festive events and medico-social organisations. Access to these events and organisations will be possible following a standard procedure. First, the Community Health Project Manager will identify a referent in each town of the COB area and obtain from that referent a list of the events and organisations likely to welcome screeners. Then the research team will contact the manager of each event or organisation to request an invitation and agree on dates, times, number of screeners needed and the number of persons expected at the event. All invitations will be collected and placed on a global schedule allowing the research team to allocate a junior researcher and a number of screeners to each event. Other voluntary medical organisations will be integrated into the screening phase on request to the research team. The number of events and organisations will be modified until the research team is able to recruit 1000 participants for the next stage. The list of events and organisations will be kept by the research team in accordance with the SPIRIT guidelines.

Every screener will be trained one full day of training. The training will include testing the tablets, the NL-IHRS, communication training and information about ethics research. Junior researchers will receive one full day of training on the same items plus screeners’ guidance.

The content installed on the REDcap© software will include inclusion and exclusion criteria, the NL-IHRS score and the appropriate brief advice.

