#### Sample size

The primary outcome will be analysed with intention-to-treat. An inter-group comparative analysis will be performed at the end of the intervention on the primary outcome. A difference in the mean NL-IHRS of 15% is expected between the intervention and the control groups. Secondary outcomes at 24 months will consist of differences in scores for quality of life (WHOQUOL-BREF), DASH questionnaire, IPAQ-short, reported smoking status, reported alcohol consumption. Tertiary outcomes, at 6- and 12-months, will consist of differences in the NL-IHRS, WHOQUOL-BREF, DASH questionnaire results, as well as the IPAQ-short, the reported smoking status and the reported alcohol consumption results.

The implementation outcomes will be the number of participants entering the groups, the number of people following the entire intervention (attendance at 75% or more of the group meetings), and the cost of the intervention.

Randomisation will be applied automatically by Redcap©.

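### Secondary endpoints are worded as change in one section and as 24-month differences without BMI in another, and are tested without baseline adjustment

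*Protocol article*

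**What the plan says.** Four parts of the protocol article bear on this point.

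- **Outcomes.** The 24-month secondary list opens with a level: "The secondary outcomes after 24 months will be quality of life, as assessed by the WHOQOL-BREF". It continues with "modification of diet, according to the DASH questionnaire" and then "modification of physical activity, following the IPAQ-short [19], BMI reduction, smoking level, modification of self-declared alcohol consumption". Diet, physical activity, BMI and alcohol are thus worded as change, and quality of life and smoking as levels. For the earlier times it says "The tertiary outcomes will be the same as previously stated, assessed at 6 and 12 months".
- **Sample size.** The same endpoints are restated: "Secondary outcomes at 24 months will consist of differences in scores for quality of life", followed by the DASH questionnaire, IPAQ-short, smoking and alcohol. BMI is in neither the secondary nor the tertiary list here.
- **Statistical methods.** Six secondary endpoints are tested with Holm-Bonferroni correction if the primary test is significant. Quantitative outcomes are compared by Student test and qualitative ones by Chi-square. A linear model adjusting for unnamed potential confounders is a secondary analysis. Power is given as about 68% per secondary endpoint.
- **Data before randomisation.** For stage 1, "The content installed on the REDcap© software will include inclusion and exclusion criteria, the NL-IHRS score and the appropriate brief advice". For stage 2, "the research team will contact each participant at intermediate cardiovascular risk to include those participants in the intervention stage", after which participants are randomised. The Abstract adds that "gauges will be used to assess BMI", without saying when.

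**The concern.** A change endpoint needs a starting value; a 24-month comparison between branches does not. The article uses both descriptions for the same endpoints. It reaches its count of six only by including BMI, which the Sample size section omits and the Outcomes section defines only as a reduction.

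Under randomisation with complete data, the expected difference between branches is the same for mean change as for the mean 24-month value. The two variables still differ in variance, and so in power and p-value. With about 20% loss to follow-up expected, they can also differ in the estimate among those who remain. These endpoints belong to a confirmatory, multiplicity-controlled step, so the choice should not stay open until the data are seen.

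The second issue is efficiency. If a pre-randomisation value exists, the planned Student test on the 24-month value ignores it. If none is collected, it cannot be recovered later. The 6-month value is no substitute, because the intensive phase of group sessions ends at day 60.

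**Working it through.** **1. The two definitions side by side**

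| Endpoint | Outcomes section | Sample size section |
|---|---|---|
| Quality of life (WHOQOL-BREF) | level | difference between groups at 24 months |
| Diet (DASH) | change | difference between groups at 24 months |
| Physical activity (IPAQ-short) | change | difference between groups at 24 months |
| BMI | reduction | not listed |
| Smoking | level | reported status |
| Alcohol | change | reported consumption |

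The Outcomes list has six entries, four of them change. The Sample size list has five. Statistical methods says six.

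**2. The plan's own figures reproduce**

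Inputs from Statistical methods: effect size 0.20, power 80%, alpha 0.05 (taken as two-sided), loss about 20%, six secondary endpoints.

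- n per branch = 2 × (1.960 + 0.842)² / 0.20² ≈ 393 by the normal formula. The t-based solution is 393.4, rounded up to 394.
- Total = 2 × 394 / (1 − 0.20) = 788 / 0.80 = 985.
- Simulated Holm step-down, six endpoints each with effect 0.20 and 394 per branch: average power per endpoint is about 68.5% if the endpoints are independent, 67.6% at correlation 0.3 between endpoints and 66.9% at 0.5. This agrees with the stated 68%, which does not include the chance of passing the primary test first.

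None of these figures depends on a baseline value.

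**3. What the choice of variable does to power**

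Assumption, not in the documents: correlation r between baseline and 24-month value of 0.3, 0.5 or 0.7. The effect of 0.20 is in units of the 24-month SD, and the SD is the same at both times.

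- Raw 24-month value: SD = 1.
- Unadjusted change: SD = √(2(1 − r)).
- 24-month value adjusted for baseline: residual SD = √(1 − r²), so the effective effect size is 0.20/√(1 − r²).

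Single test, alpha 0.05, 394 per branch:

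| r | SD of change | Power, change | Power, raw 24-month | Power, adjusted |
|---|---|---|---|---|
| 0.3 | 1.183 | 66% | 80% | 84% |
| 0.5 | 1.000 | 80% | 80% | 90% |
| 0.7 | 0.775 | 95% | 80% | 98% |

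Change and raw value break even where 2(1 − r) = 1, that is at r = 0.5. The adjusted analysis is the most powerful of the three at each r shown.

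Holm power per endpoint, six independent endpoints all with the effect and all with the same r:

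| r | Residual variance 1 − r² | Effective effect size | Holm power |
|---|---|---|---|
| no adjustment | 1.00 | 0.200 | about 68% |
| 0.3 | 0.91 | 0.210 | about 75% |
| 0.5 | 0.75 | 0.231 | about 85% |
| 0.7 | 0.51 | 0.280 | about 97% |

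The last table treats all six endpoints as quantitative. If smoking is analysed as a category, the gain in residual variance does not apply to it in this form.

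**The case against.** The strongest case on the other side is that the article is a condensed account and is merely silent on baseline. A reader might infer that none of these measures is taken before randomisation, so that four endpoints cannot be derived. The documents do not support that:

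- The software content quoted above describes the stage 1 screening tablet, used by students with the general population. Trial questionnaires would not be expected there, and the sentence does not claim to be exhaustive.
- The stage 2 inclusion contact is a separate step. What is recorded there is neither described nor ruled out.
- Outcome times are not a visit schedule. Wording such as modification or reduction suggests that a baseline exists rather than that it does not. The design figure is not shown, and a full schedule is commonly left to the full protocol.
- The endpoints as restated under Sample size, tested as under Statistical methods, can be computed without a baseline.

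All of this stands. It also stands that every participant has a pre-randomisation NL-IHRS, which allows some comparison of the branches among completers, and that the power gains in the working measure the benefit of baseline adjustment, not the damage done by the wording.

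Two things are left untouched. The article gives two definitions for the same endpoints, one of them without BMI. It also makes the unadjusted Student test the stated comparison, with adjustment only in a secondary model whose covariates are unnamed. The appeal to a later analysis plan does not remove either, because the article itself states both.

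**Conclusion.** The point holds as an inconsistency in endpoint definition together with an inefficient stated test. Four of six secondary endpoints are worded as change in one section and as 24-month differences, or not at all (BMI), in another. No baseline time is named for these instruments, and none is excluded, so nothing here shows that baseline data will be missing.

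The size depends on an assumed correlation. For r from 0.3 to 0.7, adjusting for the pre-randomisation value lifts Holm power per endpoint from about 68% to between about 75% and 97%. Reading the endpoints as unadjusted change would instead cost power below r = 0.5: 66% against 80% at r = 0.3, single test at alpha 0.05. These figures assume independent endpoints, all with effect 0.20 and equal r, and 394 analysed per branch. The primary outcome and the total of 985 are not affected.

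**What to change.** 1. Define each of the six secondary endpoints, BMI included, in the same words under Outcomes and Sample size.
2. For the quantitative ones, make the confirmatory comparison the 24-month value between branches in a linear model adjusted for the pre-randomisation value of the same measure, replacing the unadjusted Student test.
3. State that the DASH questionnaire, IPAQ-short, alcohol questionnaire, WHOQOL-BREF and BMI are recorded at the stage 2 inclusion contact before the allocation is released, if the full protocol does not already say so.

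The cost is participant time for one additional set of measures already planned for follow-up, plus setting up the forms. If the full protocol already contains the baseline assessment, the third item is one sentence. If it does not, the change has to be made before randomisation starts.

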#### Sample size

The primary outcome will be analysed with intention-to-treat. An inter-group comparative analysis will be performed at the end of the intervention on the primary outcome. A difference in the mean NL-IHRS of 15% is expected between the intervention and the control groups. Secondary outcomes at 24 months will consist of differences in scores for quality of life (WHOQUOL-BREF), DASH questionnaire, IPAQ-short, reported smoking status, reported alcohol consumption. Tertiary outcomes, at 6- and 12-months, will consist of differences in the NL-IHRS, WHOQUOL-BREF, DASH questionnaire results, as well as the IPAQ-short, the reported smoking status and the reported alcohol consumption results.

The implementation outcomes will be the number of participants entering the groups, the number of people following the entire intervention (attendance at 75% or more of the group meetings), and the cost of the intervention.

Randomisation will be applied automatically by Redcap©.

### Data collection and management

Data collection methods will use an electronic data recording system using Redcap© on mobile apps. Data storage will be on Redcap©.

Data management and data quality will be assessed by the data management unit of the CHRU Brest.

### Statistical methods

For stage 1, a descriptive epidemiological analysis will be carried out on the screened population. The total number of screenings, the distribution of the population within low-, intermediate- and high-cardiovascular risk scores, and the frequency of the modifiable risk factors listed in the score will be described.

For stage 2, the calculation of the number of subjects required is based on the comparison of the mean NL-IHRS between the two branches of the study: for a power of 80%, an alpha risk = 0.05 and an effect size (mean difference / standard deviation) of 0.20, the number of subjects required is 394 per branch. The figure of 985 subjects, including about 20% potentially lost to follow-up, should be included in the total. With the number of subjects being 394 patients per branch and the hypothesis of an effect size of 0.20 for each secondary endpoint, the test power is approximately 68% for each secondary endpoint using the Holm-Bonferroni correction to allow for multiple comparisons.

The analysis of the RCT will be conducted on an “intention to treat” basis.

No intermediate analysis will be conducted because this study leads to no biomedical risk.

A hierarchical analysis will be conducted in two steps. First, a comparison of the mean NL-IHRS between the two branches at alpha risk = 0.05 then, in the event of a statistically significant result, a comparison of the 6 secondary endpoints between the two branches, using the Holm-Bonferroni correction to consider the multiple comparisons made at this stage. In accordance with the principles of hierarchical analysis, the tests provided for in the second step will only be carried out in a demonstrative manner if the test performed in the first step is statistically significant (*p* < 0.05).

The quantitative outcomes will be compared between the two branches using a Student test. The qualitative endpoints will be compared between the two groups using a Chi-square test. Secondary, multivariate analyses will be performed using a linear model to adjust for potential confounding factors.

Missing data will be identified via the electronic CRF, and investigators will be called back to complete the data. The remaining incomplete files will be declared as lost to follow-up.

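### The intervention arm is treated in champion-led groups, but the 394 per branch and the Student test assume independent participants; any group-induced correlation erodes the stated 5% and 80%

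*Protocol article*

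**What the plan says.** Allocation is of individuals, one to one (Protocol article, abstract, Methods): "Participants will be equally randomised in two groups".

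Delivery differs between the arms (Stage 2: RCT). For the intervention arm: "Groups are expected to consist of 10 to 15 participants. The groups will meet 13 times during the 2 years of the study". A community champion leads these sessions, and champions are assigned to areas near the participants' homes. Controls receive repeated brief advice every 6 months, and no groups are described for them.

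The sample size (Statistical methods) is set "for a power of 80%, an alpha risk = 0.05 and an effect size (mean difference / standard deviation) of 0.20", from which "the number of subjects required is 394 per branch". Attrition is then added: "The figure of 985 subjects, including about 20% potentially lost to follow-up, should be included in the total".

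For the analysis, the same section says: "The quantitative outcomes will be compared between the two branches using a Student test". Categorical endpoints get a Chi-square test, and adjusted analyses a linear model. No ICC, design effect, random effect for group or champion, or cluster-robust error appears in the article.

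**The concern.** This is a partially nested design: individuals are randomised, and one arm is then gathered into groups while the other is not. Members of a group share a champion and one another's company for two years. The article treats this shared experience as part of what is being tested, since its Discussion says that group dynamics and the effectiveness of community champions are under evaluation. If some groups or champions work better than others, the 24-month scores of people in the same group will be correlated. The mean of the intervention arm then varies more than independent sampling implies.

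The Student test would use too small a standard error and give confidence intervals that are too narrow. A test that did hold 5% would have less power than planned. The primary comparison is also the sole gate to the six secondary endpoints, so a liberal first step would open the second step too often. A positive result is meant to support moving primary prevention from professionals to lay people, so the error rate of this test matters.

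**Working it through.** **Reproducing the plan's figure.** For a standardised difference of 0.20, two-sided alpha 0.05 and 80% power, the normal approximation gives n = 2 × ((1.960 + 0.842)/0.20)² ≈ 393 per arm. With the noncentral t distribution, power is 79.96% at 393 and 80.06% at 394, so 394 is exactly the independent-samples t-test answer. A one-sided test would need 310, so the plan is two-sided. Then 2 × 394 = 788 and 788/0.80 = 985. Only attrition has been added.

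**Inputs for the check**
- n = 394 analysed per arm, effect 0.20, alpha 0.05 (Statistical methods).
- Group size 10 to 15, intervention arm only (Stage 2: RCT). The midpoint is 12.5 enrolled. Because 394 is the number left after about 20% loss, the matching analysed size is 12.5 × 0.80 = 10 per group, if losses are even.
- ICC induced by group or champion: not in the document. Assumed values are 0, 0.01, 0.02 and 0.05.
- Total variance 1 in both arms; design effect 1 in the control arm.

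**Formulas** (m = analysed group size)
- Design effect, intervention arm: DE = 1 + (m − 1) × ICC.
- Variance of the contrast relative to independence: v = (1 + DE)/2.
- True standard error: SE = √((1 + DE)/394).
- Actual type I error of the Student test: 2 × (1 − Φ(1.96/√v)).
- Power of a test that holds 5%: Φ(0.20/SE − 1.96).
- Power of the Student test as planned: Φ((2.807 − 1.96)/√v), where 2.807 = 0.20 × √(394/2).

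**Results for m = 10**

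| ICC | DE | v | Type I error, Student test | Power, valid 5% test | Power, Student test as planned |
|---|---|---|---|---|---|
| 0 | 1.00 | 1.000 | 5.0% | 80.2% | 80.2% |
| 0.01 | 1.09 | 1.045 | 5.5% | 78.4% | 79.6% |
| 0.02 | 1.18 | 1.090 | 6.0% | 76.7% | 79.1% |
| 0.05 | 1.45 | 1.225 | 7.7% | 71.8% | 77.8% |

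Worked line for ICC 0.05: SE = √(2.45/394) = 0.0789; 0.20/0.0789 = 2.536; Φ(2.536 − 1.96) = 0.718. For the type I error, 1.96/√1.225 = 1.771, giving 7.7%.

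**Sensitivity to group size at ICC 0.05.** With 15 analysed per group: type I error 9.2%, valid power 67.6%. With 8 per group (10 enrolled less 20%): 7.1% and 73.6%.

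**Simulation of the Student test** (20,000 runs per setting). Type I error was 5.2% (m = 10, ICC 0.01), 7.5% (m = 10, ICC 0.05) and 9.2% (m = 15, ICC 0.05). Its power in the same settings was 79.9%, 77.9% and 77.0%. These agree with the formulas.

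**The case against.** The strongest reply is that nothing here is certain. Individuals are randomised, so if the groups have no effect on anyone, membership induces no correlation and the Student test keeps its level. Inflation requires group effects that differ yet average to zero. Nor does living in the same area produce it: neighbours are found in both arms, and a simulation with area ICCs of 0.05 and 0.10 and no treatment effect rejected in 5.2% and 5.1% of runs. All of this stands. A reader might infer that 5% and 80% definitely fail, or might insert an ordinary community ICC, or apply a cluster-trial design effect to both arms. The document supports none of these readings: only correlation produced by the group or champion counts, only in one arm, and its size is not given.

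A second reply is that the loss is small. At ICC 0.01 it is, and nothing in the article favours 0.05 over 0.01. Participants who never join a group, or attend little, stay in the intention-to-treat analysis and would dilute the correlation further.

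Third, a reader might take 72% as the power of the planned test. It is not. At its nominal level the Student test keeps about 78 to 80% in the range used; the lower figure is the power once the error rate is controlled.

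The reply that an unseen analysis plan may deal with clustering carries less weight. The article itself fixes both the sample size and the test, and both rest on independence.

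**Conclusion.** The point holds in conditional form. The arithmetic behind 394 and 985 is correct; the weakness is the assumption of zero within-group correlation in an arm whose groups and champions are themselves being evaluated. For any positive group-induced ICC the direction is certain: the Student test's standard error is too small, and a valid 5% test has less than 80% power at 394 per branch. The size is not certain. With about 10 analysed per group and an assumed ICC of 0 to 0.05, type I error runs from 5.0% to 7.7% and valid power from about 80% down to 72%. The upper group size of 15 with ICC 0.05 gives about 9% and 68%.

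These figures assume equal total variance in the arms, even losses across groups and one level of grouping. A champion leading several groups could add to the correlation, but the article gives no number of champions. The secondary and tertiary comparisons share the independence assumption, but their ICCs may differ and no size is claimed for them.

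**What to change.** - Make the primary analysis a partially nested linear mixed model: a random group effect in the intervention arm only, arm-specific residual variances and small-sample degrees of freedom. Cluster-robust standard errors are an acceptable alternative. About 39 groups (394/10) would be available.
- Add a champion effect only if champions lead more than one group; otherwise it cannot be separated from the group effect.
- Use the same approach for the other outcomes, with a suitable model for the categorical ones.
- Make sure that group and champion identifiers are in the dataset. The article does not say whether they are.
- Replace the flat 80% with the power of 394 per branch over a stated ICC range that includes 0: about 72 to 80% for ICC 0.05 to 0 with 10 analysed per group.

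The cost is analysis wording, at most a data field or two, and a slightly less favourable stated power. No extra participants are needed, though keeping 394 means accepting that power and does not restore 80% if the ICC is positive.

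### The 68% power stated for each secondary endpoint leaves out the primary gate and is not labelled so; with the gate it is about 55% to 64%, depending on an unstated correlation

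*Protocol article*

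**What the plan says.** All the relevant statements are in the Statistical methods section of the protocol article.

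- **Primary sizing:** the calculation is made "for a power of 80%, an alpha risk = 0.05 and an effect size (mean difference / standard deviation) of 0.20", and "the number of subjects required is 394 per branch". The total then follows: "The figure of 985 subjects, including about 20% potentially lost to follow-up, should be included in the total".
- **Secondary power:** with the same number per arm, and a hypothesised effect of 0.20 on each secondary endpoint, "the test power is approximately 68% for each secondary endpoint using the Holm-Bonferroni correction to allow for multiple comparisons".
- **Testing order:** the primary endpoint is tested first, at the 0.05 level. The second step depends on that outcome and is described so: "then, in the event of a statistically significant result, a comparison of the 6 secondary endpoints between the two branches". Holm-Bonferroni applies to this family. The section adds that the second-step tests count as confirmatory only when the first-step test is significant.

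The sentence on secondary power names one adjustment, the Holm correction. It does not mention the gate and does not say that the figure is conditional on passing it.

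**The concern.** The plan describes a two-step procedure. A secondary endpoint gives a confirmatory result only if two things happen: the primary is significant, and the endpoint is rejected under Holm. The primary itself fails in about one trial in five under the planning assumptions. A power figure that reflects only the second requirement overstates what the whole procedure delivers, unless it is labelled as a second-step figure.

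The six secondary endpoints (quality of life, diet, physical activity, BMI, smoking, alcohol) carry the behavioural side of the trial's message. A reader who takes 68% as the design's power for each would put the chance of missing a real effect of the assumed size at 32%. Under the procedure as planned it is 45% with independent endpoints and 38% at a correlation of 0.7.

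**Working it through.** **Inputs from the Statistical methods section:** 394 evaluable participants per arm; effect size 0.20 for the primary and for each secondary endpoint; alpha 0.05; six secondary endpoints; Holm within the secondary family; gate at primary p < 0.05. Equal allocation is stated in the abstract: "Participants will be equally randomised in two groups".

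**Assumptions:** tests are two-sided (sidedness is not stated, but two-sided testing reproduces 394). Each test statistic is approximately normal. One common correlation links all seven endpoints. The document gives no correlations, so a range is shown.

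**Step 1. Reproduce the primary sizing.**
- n per arm = 2 × (1.960 + 0.842)² / 0.20² ≈ 393 by the normal formula, and 394 with the t-test.
- Power at 394 per arm is 80.2% (80.1% by noncentral t).
- Total: 2 × 394 = 788, and 788 / 0.8 = 985. These figures agree with the plan.

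**Step 2. Reproduce the 68%.** The noncentrality of each test is 0.20 × √(394/2) = 2.807. The Holm step-down on six such tests was simulated with 300,000 runs, with all six effects at 0.20 and no gate.
- Power per endpoint is 68.5% if independent, 67.6% at correlation 0.3 and 66.9% at 0.5.
- Plain Bonferroni at 0.05/6 gives 56.7%.

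The plan's figure is therefore Holm power with all six effects real and the secondary step always carried out.

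**Step 3. Add the gate.** An endpoint now counts only if the primary has p < 0.05 *and* Holm rejects the endpoint. Under independence this is a product: 0.685 × 0.80 = 0.55. Under correlation it comes from the simulation:

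| Common correlation (assumed) | Holm only, no gate | Including the gate | Given that the gate is passed |
|---|---|---|---|
| 0 | 68.5% | 54.9% | 68.5% |
| 0.3 | 67.6% | 58.0% | 72.5% |
| 0.5 | 66.9% | 60.0% | 74.9% |
| 0.7 | 66.3% | 62.5% | 78.0% |
| 0.9 | 64.7% | 64.0% | 79.9% |

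The last column is the third divided by the power of the gate; for example, 62.5 / 80.2 = 78%. Repeat simulations agreed within about 0.2 percentage points.

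**Step 4. Check the direction.** The gated event is a subset of the ungated one, so adding the gate can only lower the figure. Letting the primary correlate more strongly with the secondaries than they do with each other does not change the conclusion: 0.5 among the secondaries and 0.6 with the primary gives 61.8%. The largest gated value examined is 64.0%.

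**Step 5. Optional sensitivity.** If only one of six independent endpoints is truly affected, its power is 56.8% without the gate and 45.6% with it.

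**The case against.** The strongest reply is that nothing has been miscalculated. The 68% follows from the stated inputs. It describes the Holm step, and the gate is set out openly in the same section. Read as power given a significant primary, 68% is right under independence and conservative under positive correlation (72.5% at 0.3, 78% at 0.7). Quoting second-step power for a gated family is a legitimate convention. The sample size rests on the primary alone, so no design decision depends on this figure.

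Most of that stands, and it rules out several stronger readings:

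- **An arithmetic error.** A reader might infer one; the figure reproduces, so there is none.
- **A hidden assumption that all six effects are real.** The plan states an effect of 0.20 on each secondary endpoint as its hypothesis. The 46% for a single affected endpoint replaces that hypothesis with another, so it is a sensitivity figure and not a fault in the plan.
- **The all-six assumption as a cause of the 55% to 64% range.** It is not. That range comes from the gate alone, with all six effects still real.
- **Null secondaries bound to be misread.** If the gate fails, the plan already denies the secondary tests confirmatory status. If it is passed, the conditional power is the relevant one, and that is 68% or higher at the non-negative correlations examined.

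What the reply does not answer is the missing label. The sentence presents 68% as the power for each secondary endpoint with Holm as its only qualification, in a section whose procedure also requires a significant primary.

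**Conclusion.** The point holds as one of labelling and completeness. The 68% is the Holm power for six endpoints, all at 0.20, before the gate. It is not the probability that the planned procedure gives a confirmatory result on a given endpoint. That probability is about 55% if the endpoints are independent, 58% at a common correlation of 0.3, 62% at 0.7 and 64% at 0.9. The shortfall against 68% is thus about 13 points at independence and about 4 at a correlation of 0.9.

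The direction does not depend on the correlation, but the size does, and the document gives no value. Some positive correlation with the primary is plausible, because the abstract says that smoking level is assessed by the NL-IHRS scoring system. The figures also rest on two-sided tests, 394 evaluable participants per arm and an effect of exactly 0.20 on the primary and on all six secondaries. The point gives no ground for calling the sample size or the testing procedure wrong.

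**What to change.** Replace the sentence on secondary power with wording such as:

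*About 68% for each secondary endpoint under Holm, before the primary gate, if all six effects are 0.20; including the requirement of a significant primary result, about 55% if the endpoints are independent, rising to about 62% at an assumed correlation of 0.7.*

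State the assumed correlation next to any gated figure. Do not describe the 68% as conditional on a significant primary and set it beside the 62%: a conditional 68% belongs to independence, where the gated figure is 55%, while at a correlation of 0.7 the conditional figure is about 78%. A figure for fewer than six real effects may be added as a sensitivity case but is not required.

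The cost is one sentence and a less favourable number. The 394 per arm, the total of 985, the tests and the error control all stay as they are.
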